#### Reasoning

The sample size of the Nijmegen pilot study was small (N = 12) [19]. Powerful within-subjects analyses revealed high effect sizes in post-treatment (η^2^_p _= 0.8, p < 0.01) and delayed assessment (η^2^_p _= 0.5, p = 0.01). In order to avoid bias from carry-over effects between the groups potentially occurring in a within-subjects design, in the present trial a between-subjects design will be conducted and the interaction effect between groups and measurement points T_0 _(Baseline) and T_2 _(16 weeks after baseline) will be analysed as primary endpoint. The between-subjects design will reduce the statistical power, consequently more subjects are needed. Furthermore, the correlation of r = 0.85 between the measurements in control and treatment groups as stated in the meta-analysis of Kessels et al. is quite large [18]. However, they excluded trials with between-subjects design and only analysed studies using within-subjects design. Considering that group differences might be influenced by several unknown confounders in our real-life setting at the patient's home we assume a correlation of r = 0.6 for the power calculation. Although the meta-analysis demonstrated large effect sizes (d = 0.87), it also found large confidence intervals (CI95% = 0.10-1.64). It is assumed that detecting even small effects is reasonable, because the implementation of relearning techniques will be a low-cost and a low-risk intervention. For these reasons, we performed a conservative power calculation, which is able to detect even small effect sizes for the interaction. The patients' planned trial flow is shown in Figure 1.

**Figure 1 F1:**
[figure not shown]
**Trial flow**. ELL = Errorless Learning; TEL = Trial and Error Learning.

### Randomisation and Blinding

The trial statistician at a detached site will provide a 1:1 randomisation block-wise without stratification via e-mail for each individual case after recruitment and upon request of the site investigator. Independent assessors are blinded to group assignment. Following the nature of the intervention, participants are not blind for the type of intervention. However, neither the patients nor the interventionists will be explicitly presented an assumption as to which intervention may be more likely to improve activities of daily living. Moreover, both interventions include the same amount of personal involvement which prevents contrasting interventions with waiting group scenarios or grossly reduced personal involvement. Blinded assessment of the treatment effects will be achieved by videotaping the performance of the patient and removing all hints of prior treatment modality.

### Statistical analysis

Baseline measures and demographics of participants significantly differing at baseline in ELL and TEL group as well as control measures are used as co-variates in an analysis of variance. The primary intention-to-treat analysis will be compared with a per-protocol analysis.

The method "Last Observation Carried Forward" will not be used for the imputation of missing data, because it introduces bias in dementia research [20]. If necessary, the Full Information Maximum Likelihood method will be applied for data replacement [21,22]. Drop-out analysis will be performed comparing all baseline and control measurements and follow-up data of participants and dropouts as far as sufficient data are available. Therefore participants are asked to give consent to a final assessment using the Task Performance Scale at the dropout time point. Furthermore, the carers are asked to fill in the Interview for Deterioration in Daily Living Activities in Dementia at all measurement time points as planned.

The comparison of ELL and TEL group will be adjusted for baseline imbalance and process variations. Variations in treatment integrity, medication of achetylcholinesterase inhibitors, and study sites will be considered as possible mediating variables and analysed with hierarchical linear models. All statistical tests will be two-sided on an alpha level of 0.05.

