### Outcome

The primary outcome is the performance of the two selected and trained daily living tasks. The applied measurement is the Task Performance Scale. It demonstrated feasibility and responsiveness within the pilot trial. The evaluation of task performance by measuring the number of occurring errors or the number of insufficient task performances is an established standard in trials on relearning cognitive or daily living tasks. Patient's task performance will be video recorded by the interventionist, in order to assure blinded rating and to avoid that the patient will have potentially confusing contacts with several different persons. Blinded assessors from the REDALI-DEM headquarters in Freiburg will rate the videos regarding the number of occurring errors and steps performed insufficiently. Table 2 shows the primary and the secondary outcomes including measurement instruments and time points. Secondary outcome and control measures are performed by the study physician during the patient's visit at the study site, except the Verbal Rating Scale for the satisfaction with the intervention, which is applied by the interventionists at the patient's home.

**Table 2 T2:** Measurement scheme including primary and secondary outcome

Weeks	0		11		16*		19-20		26
Measurement time points	t_0_		t_1_		t_2_				t_3_
Intervention		12 sessions		break		break	refresher	break	
Primary outcome									
Task Performance Scale (Rating of assessment video)	x		x		**x**				x

Secondary outcomes									
Satisfaction with intervention (Verbal Rating Scale)		each session					each session		
Activities of daily living (Interview for Deterioration in Daily Living Activities in Dementia)	x				**x**				x
Resource utilisation (Resource Utilisation in Dementia)	x				**x**				x

Control measurements									
Cognition (Mini Mental State Examination)	x				x				x
Course of Dementia (Clinical Dementia Rating)	x				x				x
Challenging behaviour (Neuropsychiatric Inventory, 12 items questionnaire)	x				x				x
Socio-demographic data	x								
Depression (Geriatric Depression Scale, 15 items)	x								
Attention (Trail Making Test)	x								
Intervention adherence (rating of treatment videos)		selected sessions							

* Primary measurement time point

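### Part of the covariate set for the primary analysis is chosen by baseline significance tests, so the model is not fixed in advance and precision is lost

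*Protocol article*

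**What the plan says.** The Statistical analysis section names two groups of covariates in one sentence. The first is conditional on a test: "Baseline measures and demographics of participants significantly differing at baseline in ELL and TEL group". The second follows directly and carries no condition: "as well as control measures are used as co-variates in an analysis of variance". Later the section adds: "The comparison of ELL and TEL group will be adjusted for baseline imbalance and process variations".

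Table 2 (Outcome section) shows what falls where. Its control measurements are the MMSE, Clinical Dementia Rating, Neuropsychiatric Inventory, socio-demographic data, Geriatric Depression Scale, Trail Making Test and intervention adherence. The Task Performance Scale is the primary outcome. The daily-living interview and resource utilisation are secondary outcomes. All three are measured at week 0, and none is a control measurement.

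The Reasoning subsection under Sample Size sets the primary contrast as "the interaction effect between groups and measurement points" T0 and T2. Site is treated separately: "study sites will be considered as possible mediating variables and analysed with hierarchical linear models".

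**The concern.** After randomisation, any baseline difference between the arms is due to chance. A significance test therefore cannot show which variables deserve adjustment. It picks those that happen to be imbalanced, whether or not they predict the outcome, and passes over predictive ones whose imbalance falls short of p < 0.05.

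Two things are at stake. The composition of the primary model depends on the observed data. And the gain in precision from adjusting for a known predictor is realised only in the few trials where that predictor crosses the threshold. The article states this rule outright, so it is not a detail left to an analysis plan; a plan that followed the article would inherit it.

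**Working it through.** **Inputs from the Sample Size section:** f = 0.10, correlation 0.6, two groups, two measurements, two-sided alpha 0.05, N = 160 (80 per arm), λ = 8.00, critical F = 3.901 on 1 and 158 df. **Assumed, because the article gives no value:** correlations of 0.3 and 0.5 between another covariate and the change score, and the number of baseline tests.

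**1. The plan's own figure.** λ = f² × N × m / (1 − r) = 0.01 × 160 × 2 / 0.4 = 8.00. Critical F(1, 158) = 3.901 and power is 0.803; 160 is the smallest even N that reaches 80%. The stated sample size reproduces exactly. On the outcome's SD scale, f = 0.10 is a difference in change of 4 × 0.10 = 0.40 SD, with SD of change √(2 × 0.4) = 0.894.

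**2. Chance of entry.** Each tested variable enters in 5% of trials. The chance that at least one of k independent tests is significant is 1 − 0.95^k:

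| k | chance |
|---|---|
| 3 | 14% |
| 5 | 23% |
| 8 | 34% |
| 10 | 40% |

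Three corresponds to the week-0 scales in Table 2 that are not control measurements. Correlated variables would change these figures.

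**3. T0 task performance.** It is already one level of the group-by-time contrast, which is equivalent to analysing the change score. Entering it as a covariate as well turns the analysis into ANCOVA. By normal approximation at 80 per arm:
- Change score: SE = 0.894 × √(2/80) = 0.141, ratio 0.40 / 0.141 = 2.83, power about 0.807.
- ANCOVA: residual SD = √(1 − 0.36) = 0.80, SE = 0.80 × √(2/80) = 0.126, ratio 0.40 / 0.126 = 3.16, power about 0.885.

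Simulation of the planned contrast (80 per arm, 40,000 runs):

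| T0 as covariate | power | type I error |
|---|---|---|
| never (interaction alone) | about 80% | about 5% |
| only if significantly different | about 81% | about 4.5% |
| always | about 88% | about 5% |

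**4. What happens near the threshold.** A baseline difference is significant at about 1.975 × √(4/160) = 0.312 SD. An imbalance of 0.30 SD stays below this, so no adjustment is made. Because T2 follows T0 with slope 0.6, the change contrast is then off by (1 − 0.6) × 0.30 = 0.12 SD, against the arm that started higher. That is 0.12 / 0.40 = 30% of the planned effect. Slightly above 0.312 SD, the estimator switches to the adjusted one and this shift is removed.

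**5. Another covariate under the rule, such as the baseline daily-living score.** Simulation with 20,000 runs and N = 160:

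| assumed correlation with change | power: never | under the rule | always | type I error under the rule |
|---|---|---|---|---|
| 0.3 | 0.80 | 0.81 | 0.84 | 0.051 |
| 0.5 | 0.80 | 0.81 | 0.90 | 0.043 |

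The covariate entered in about 5% of runs, so nearly all of the gain is lost.

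**6. Demographics.** Table 2 lists "Socio-demographic data" among the control measurements, which enter unconditionally. The Statistical analysis section makes demographics conditional on a significant difference. Both cannot apply.

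**The case against.** A reader who stops at the conditional clause might infer that no covariate enters without a significant baseline difference, and that strong predictors such as the MMSE are therefore left out. The text does not support that. The same sentence brings in the control measures without a test, and Table 2 places cognition, dementia severity, behaviour, depression and attention among them. Site is not left out either: the Setting section promises control for site effects, and the analysis section assigns site to hierarchical models.

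A reader might also infer that T0 task performance is ignored unless it is imbalanced. It is not, because it is a level of the primary contrast. Calculations based on an unadjusted week-16 score would overstate the loss, since the plan does not use that analysis. It is also fair to say that most of the step from 80% to 88% is the general advantage of ANCOVA over a change score. What remains is that this plan allows the T0 covariate in only when a baseline test is significant, and so captures about one percentage point of that gain.

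Finally, a reader might suspect more false positives. The simulations show none: the two-step rule is at nominal level or slightly conservative.

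These objections narrow the point but do not remove it. The stated 80% power at N = 160 does not depend on the rule.

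**Conclusion.** The concern holds for part of the covariate set: baseline measures off the control list and, because of the conflict with Table 2, possibly demographics. For these, the plan selects on chance, leaves the primary model open until the data are seen, and switches estimator at a T0 imbalance of about 0.31 SD.

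The cost is lost precision. Power is about 81% instead of 88% for T0 task performance, and about 0.81 instead of 0.84 to 0.90 for another covariate. In addition, a shift of up to about 0.12 SD goes uncorrected in trials with a T0 imbalance just under the threshold. That shift is conditional on the observed imbalance; over repeated randomisations the change contrast is unbiased.

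The T0 figures rest on the protocol's own r = 0.6 and f = 0.10 with no true baseline difference. The other range rests on assumed correlations of 0.3 to 0.5. Inflated type I error and omission of the MMSE or site are not part of this finding.

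**What to change.** Delete the significance condition. Name the baseline covariates in advance on prognostic grounds and include them whatever their balance: the T0 Task Performance Scale as an ANCOVA covariate and the T0 Interview for Deterioration in Daily Living Activities, alongside baseline values of control measures such as the MMSE, and site. State one rule for demographics that agrees with Table 2. Replace the general reference to adjusting for baseline imbalance with this list, and describe baseline balance without p-values.

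The cost is a sentence or two in the Statistical analysis section. Every listed variable is already available at week 0, and N = 160 stands.

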#### Exclusion criteria

• Major depression, Geriatric Depression Scale (15 items) ≥ 9.

• Major need of physical nursing care (level 2 or higher according to the German Long-Term Care Insurance Act indicated by 120 min or more per day).

• Severe behavioural disturbances, unstable medical conditions or lack of attention and understanding of simple task instructions in German language, which do not allow participation in the study as judged by the recruiting study physician.

• Involvement in other clinical trials.

• In order to achieve the recruitment of a naturalistic sample, there will be no limitation on drug therapy. During the trial duration, drug treatment should be kept as constant as it is appropriate for an optimal routine medication management. Within the statistical analysis, we will control for possible changes in anti-dementia drug treatment in both groups.

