Each interventionist of the ELL and the TEL condition and each substitute interventionist must apply 12 sessions to two pilot patients. The third and tenth relearning session with each pilot patient must be video recorded. The Dutch supervisors will use these video tapes to assess the quality of the treatment and to reflect on possibilities for improvement within the repetition seminar. Interventionists will receive certification based on the quality of their pilot treatment and their contribution within the repetition seminar. In order to monitor the treatment adherence during the study phase, the main ELL and TEL interventionist must provide video tapes with two tasks of the third and tenth relearning sessions with their first patient. The focus of the treatment adherence will be the interventionists' anticipation of and reaction on the patient's errors. Criteria will be specified in the treatment manuals. In cases of inappropriate treatment adherence the interventionist will receive an intensive telephone mentoring session. Continuing insufficient adherence will lead to the interventionist's replacement.

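### The stated ELL-TEL comparison is adjusted for process variables and for control measures not restricted to baseline, so the intention-to-treat contrast may be biased in either direction

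*Protocol article*

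**What the plan says.** The Reasoning subsection under Sample Size names the group-by-time interaction from T0 to T2 (week 16) as the quantity that "will be analysed as primary endpoint". The Statistical analysis section adds the population: "The primary intention-to-treat analysis will be compared with a per-protocol analysis".

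The same section sets out the adjustment in three places:

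- Baseline measures and demographics that differ significantly between arms "as well as control measures are used as co-variates in an analysis of variance". No time point is attached to the control measures.
- "The comparison of ELL and TEL group will be adjusted for baseline imbalance and process variations".
- Treatment integrity, acetylcholinesterase inhibitor medication and study site "will be considered as possible mediating variables and analysed with hierarchical linear models".

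Table 2 (Outcome section) defines the control measurements. MMSE, CDR and NPI are taken at t0, t2 and t3. Socio-demographic data, the Geriatric Depression Scale and the Trail Making Test are taken at t0 only. The last row, "Intervention adherence (rating of treatment videos"), has entries only for selected sessions during treatment.

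The list of exclusion criteria, in its item on drug therapy, adds that "we will control for possible changes in anti-dementia drug treatment in both groups".

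On how adherence is measured in the study phase, the Intervention adherence section says that "the main ELL and TEL interventionist must provide video tapes with two tasks of the third and tenth relearning sessions with their first patient".

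**The concern.** An intention-to-treat contrast estimates the total effect of being assigned to ELL rather than TEL. Randomisation protects that contrast only while the model conditions on nothing that assignment could have changed. The article sets process variations beside baseline imbalance as a second class of adjustment, so the term cannot mean baseline values. It then calls two of the variables, integrity and medication, possible mediators, which means variables on the path from treatment to outcome.

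Two kinds of bias are possible. If part of the effect runs through the adjusted variable, that part is removed. If the adjusted variable and task performance share an unmeasured cause, and the arm shifts the variable, a spurious arm difference can appear where none exists.

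For NPI the article itself supplies a reason to expect an arm difference. The Ethical Considerations section says TEL patients will meet failure more often and foresees cases of severe behavioural disturbance. Yet NPI is classed as a control measure, and no comparison of it between arms is listed among the outcomes.

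Study site is also placed among the mediators. It is fixed before randomisation, so it cannot be one; it is an ordinary covariate.

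**Working it through.** **1. Which covariates could be affected by assignment**

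| Variable | When measured | Admissible in the primary model? |
|---|---|---|
| Socio-demographics, GDS, Trail Making | t0 only | yes |
| MMSE, CDR, NPI | t0, t2, t3 | t0 value yes, later values no; the text does not say which |
| Intervention adherence / treatment integrity | during treatment only | no |
| Changes in anti-dementia drugs | during the trial | no |
| Study site | before randomisation | yes |

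For adherence and drug changes no baseline reading is available. For MMSE, CDR and NPI the fault is a missing restriction to t0.

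**2. The plan's own figure**

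Inputs from the Sample Size section: f = 0.10, two groups, m = 2 measurements, r = 0.6, alpha 5%, N = 160.

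λ = f² × N × m / (1 − r) = 0.01 × 160 × 2 / 0.4 = 8.00, with df 1 and 158 and critical F = 3.901. The noncentral F distribution gives power 0.803. The stated figure is reproduced. At N = 175, λ = 8.75 and power is 0.837.

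On the outcome scale, f = 0.10 corresponds to a difference in change of 4f = 0.40 SD. The variance of change is 2(1 − r) = 0.8 in SD² units. Equivalently, λ = (N/4) × δ² / variance = 40 × 0.16 / 0.8 = 8.00.

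**3. Part of the effect runs through the covariate, error variance unchanged**

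The share p is an assumption; the documents give none. Then λ = 8.00 × (1 − p)².

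| p | λ | Power, N = 160 | Power, N = 175 | N for 80% power |
|---|---|---|---|---|
| 0 | 8.00 | 0.80 | 0.84 | 160 |
| 10% | 6.48 | 0.72 | 0.75 | 196 |
| 20% | 5.12 | 0.61 | 0.65 | 248 |
| 30% | 3.92 | 0.50 | 0.54 | 324 |

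**4. The covariate also explains outcome variance**

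Assume the arm shifts the covariate by a SD and the covariate has coefficient b on performance. The adjusted effect is 0.40 − ab and the residual variance of change is 0.8 − b².

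| a, b | Adjusted effect | λ and power, variance 0.8 | λ and power, variance 0.8 − b² |
|---|---|---|---|
| 0.1, 0.3 | 0.37 | 6.85, 0.74 | 7.71, 0.79 |
| 0.2, 0.5 | 0.30 | 4.50, 0.56 | 6.55, 0.72 |
| 0.3, 0.5 | 0.25 | 3.13, 0.42 | 4.55, 0.56 |

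The last column is the consistent one under this model. With the opposite sign (a = −0.1 to −0.3, b = 0.5) the adjusted effect is 0.45 to 0.55, so the effect is inflated instead.

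**5. No true effect, shared unmeasured cause**

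Assume a loading of 0.6 on the shared cause for both covariate and change. The expected bias is −a × 0.6² × √0.8, that is −0.06, −0.10 and −0.16 SD for a = 0.2, 0.3 and 0.5. Simulation at N = 160 (4,000 runs each) gave −0.06, −0.09 and −0.16, with two-sided type I error of about 0.08, 0.11 and 0.22. The unadjusted analysis stayed near 0.05. With a = 0 the adjusted analysis had type I error 0.049, so no bias.

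**6. Coverage of the adherence rating**

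Seven sites × 2 main interventionists × 1 first patient = 14 patients, or 14/175 = 8% of the planned sample.

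**The case against.** The strongest reply is that the primary model is ambiguous rather than wrong. The sample size rests on a two-group, two-measurement ANOVA with denominator df of 158, which contains no covariates. The sentence on mediating variables can be read as a secondary analysis. The drug-therapy item does not say that the control takes place in the primary model. Covariate time points are commonly left to the analysis plan, and this is a condensed article.

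This stands in part. A reader might infer that the article commits to week-16 MMSE, CDR and NPI as covariates; it does not, since t0 values exist and no time point is given. The reply fails on the core. The df of 158 belongs to the sample size calculation, and no section describes an unadjusted or baseline-only primary model. The sentence on process variations concerns the ELL-TEL comparison itself.

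Four further stronger readings are not supported:

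- **That the adjustment must shrink the effect.** Both arms are active with equal contact, and nothing in the article shows that the arm shifts MMSE, CDR or prescribing. Without a shift this bias is absent, and with one its sign is open.
- **That power would fall to 42%.** That figure ignores the variance the covariate explains. Under the same assumptions the consistent value is about 56%.
- **That integrity is missing for 92% of patients.** This holds only if it is used as a patient-level covariate, which the article does not say. The rating concerns the interventionist and could enter a hierarchical model at that level.
- **That NPI is the only channel for behavioural harm.** The Monitoring and Safety sections provide for adverse-event handling and reporting. NPI is the behavioural scale in Table 2, and its use as a covariate would not prevent it from being reported.

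**Conclusion.** The point holds in a limited form. As written, the comparison of arms is adjusted for process variables, and the control measures used as covariates are not confined to t0. One of them, adherence, cannot be a baseline variable. This may remove part of the intention-to-treat effect or otherwise bias it in either direction, provided that the arm affects the covariate.

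The size is unknown from the documents. As an illustration, if 10% to 30% of the assumed effect ran through the covariate and error variance were unchanged, power at N = 160 would be about 72% to 50% instead of 80%; the loss is smaller if the covariate also reduces error variance. Under a different assumption, a shared cause with no true effect, type I error could rise to roughly 0.08 to 0.22. Listing site as a mediator is a labelling error, because adjusting for site is legitimate. The sample size calculation is correct and not affected.

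**What to change.** State that the primary model (group by time, t0 to week 16, intention-to-treat) contains only variables measured before randomisation: t0 values of the control measures, and study site as an ordinary covariate. Remove process variations, adherence, post-baseline control measures and drug changes from that model, and place them in separately labelled secondary or mediation analyses. Use the study-phase adherence rating at interventionist level at most, not as a patient-level covariate. Compare NPI at weeks 16 and 26 between arms, because the Ethical Considerations section anticipates behavioural disturbance under TEL.

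The cost is a little extra analysis wording. NPI is already scheduled at both visits, so no new data are needed. With the primary model so restricted, the stated design keeps its power of 0.803 at N = 160 (0.837 at N = 175), before any gain in precision from baseline covariates.

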**Methods/Design:**

A seven-centre single-blind, active-controlled design with a 1:1 randomisation for two parallel groups will include 175 persons diagnosed with Alzheimer's disease or mixed type dementia (MMSE 14-24), living at home, showing at least moderate need for assistance in instrumental activities of daily living; primary carer available and informed consent of patient and primary carer. Patients of both study arms will receive 15 one-hour-sessions at home by trained interventionists practising two daily living tasks individually selected. In one group the trial and error technique and in the other group the errorless learning method will be applied. Primary outcome is the task performance measured with the Task Performance Scale six weeks post treatment.

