a. The interventionist asks the patient to perform the task. Cue cards are not provided.

b. When the patient makes an error, he is allowed up to three guesses (or a maximum of 30 seconds without guess) to correct on his own.

c. If the participant is unable to perform the step correctly, the interventionist will use different questions relative to the purpose of the task, in order to help the patient to find solutions.

d. If the participant is still unable to perform the step correctly, the interventionist will give the correct verbal instruction - but no demonstration - of what is to do next, so that the patient can perform the step correctly.

e. These procedures of patient's performance incl. guessing, interventionist's helping questions and - if necessary - correct instructions are followed until the whole task is performed.

f. The training will stop after 30 min, no matter how many steps of the tasks the patient has performed. When the patient performed the task in less than 30 min training, the same task is trained again, but not more than twice.

Final intervention session (same procedure in ELL and TEL group)

Video tapes of baseline task performance

a. Task I: The interventionist again video records the performance without giving any cue or instruction.

b. Task II: The same procedure.

Assessment sessions

The interventionist must video record the patient's task performance at measurement time point T_2 _(16 weeks after baseline) and T_3 _(26 weeks after baseline). In the assessment visits, he has to follow the same procedures as in the final intervention session.

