### Ethical Considerations

In the trial and error condition, individuals will benefit from the trial and error learning, but will be exposed to the risk of experiencing deficits through insufficient task performances more frequently than individuals in the errorless condition. For cases where these experiences lead to severe behavioural disturbances the trial will be discontinued. If the ELL intervention proves to be superior to the trial and error learning, the errorless learning approach will reduce the experience of insufficient task performances in AD patients. In all cases, the closest caring relative of the patient will be asked to give assent to support the trial procedures by filling in forms and arranging appointments. Patients who are not able to consent will be included, if a legally appointed representative gives consent.

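### The protocol does not expressly keep the week-16 video for patients who drop out before then, so their primary outcome is left to a missing-at-random assumption

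*Protocol article*

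**What the plan says.** The abstract fixes the endpoint: "Primary outcome is the task performance measured with the Task Performance Scale six weeks post treatment". In the intervention scheme this is T2, week 16, and the sample-size reasoning makes the group-by-time interaction from baseline to T2 the primary endpoint. The general filming rule, under Intervention sessions, is that "The interventionist must video record the patient's task performance at measurement time point" T2 and again at T3.

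The Statistical analysis section then says four things that bear on dropouts:

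- Analysis set: "The primary intention-to-treat analysis will be compared with a per-protocol analysis".
- Missing data: last observation carried forward is rejected, and "If necessary, the Full Information Maximum Likelihood method will be applied for data replacement".
- Drop-out analysis: "Drop-out analysis will be performed comparing all baseline and control measurements and follow-up data of participants and dropouts as far as sufficient data are available". To serve it, "participants are asked to give consent to a final assessment using the Task Performance Scale at the dropout time point".
- Carers: "the carers are asked to fill in the Interview for Deterioration in Daily Living Activities in Dementia at all measurement time points as planned".

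The Ethical Considerations section states that patients in the trial-and-error arm (TEL) will meet failed performance more often than those in the errorless arm (ELL), and adds: "For cases where these experiences lead to severe behavioural disturbances the trial will be discontinued". I read this as ending the individual patient's participation.

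**The concern.** After dropout, the secondary carer-rated outcome keeps its calendar, while the primary outcome is mentioned only as one last assessment at the time of leaving. If sites follow that text, a patient who leaves before week 16 has no observed T2 value. No later analysis plan can recover a video that was never filmed.

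The dropout-time video does not measure the same thing as T2. Taken during the first training block, it reflects an incomplete course of sessions and no retention interval. Taken between weeks 11 and 16, it reflects a shortened interval. The trial's question is performance six weeks after the intervention.

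The intention-to-treat contrast would then depend, for these patients, on FIML being valid under missing at random. The protocol itself describes a way of leaving that follows from failure at the task and is likelier in one arm. If the unseen TEL scores were worse than the model predicts, TEL would look better than it is and an advantage of ELL would be understated.

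**Working it through.** **1. What is provided for a patient who drops out before week 16**

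| Measure | Status | Provision after dropout |
|---|---|---|
| Task Performance Scale (video) | Primary | One final assessment at the time of dropout, by consent |
| Carers' daily-living interview | Secondary | All planned time points |

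The T2/T3 filming rule under Intervention sessions is general and does not mention dropouts. The words chosen for the dropout assessment (final, and dated to the dropout) point to it as the last video. That is an inference: the article neither forbids nor confirms a week-16 video for these patients.

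**2. Who is affected**

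- Leaves in weeks 1 to 10: T2 not observed; dropout-time video falls within training.
- Leaves between weeks 11 and 16: T2 not observed; retention interval shortened.
- Leaves between weeks 16 and 26: T2 already observed, so the primary outcome is not affected.

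**3. The plan's own sample size**

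Inputs from the Sample Size section: f = 0.10, two measurements (m = 2), correlation ρ = 0.6, α = 0.05 (two-sided per Statistical analysis), power 80%, N = 160.

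For the group-by-time interaction, λ = f² × N × m / (1 − ρ) = 0.01 × 160 × 2 / 0.4 = 8.00. With 1 and 158 degrees of freedom the critical F is 3.901, and the noncentral F gives power 0.803. The plan's figures reproduce; the sample size is not at fault.

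**4. What loss the recruitment target covers**

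The abstract gives 175 patients. 175 − 160 = 15, and 15/175 = 8.6%. The article states no dropout rate and does not say that the 15 are a dropout allowance; that is inferred.

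**5. Complete-case power at assumed losses of T2**

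Same formula, with N equal to 175 × (1 − loss), rounded down:

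| Assumed loss | N with T2 | λ | Power |
|---|---|---|---|
| 5% | 166 | 8.30 | 0.817 |
| 8.6% | 160 | 8.00 | 0.803 |
| 10% | 157 | 7.85 | 0.795 |
| 15% | 148 | 7.40 | 0.771 |
| 20% | 140 | 7.00 | 0.748 |
| 30% | 122 | 6.10 | 0.688 |

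These rates are illustrations. The power loss is moderate and secondary to the reliance on missing at random.

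**6. Bias**

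If only the TEL side departs from the model, the bias in the arm difference is roughly the excess proportion of missing T2 values in TEL times the gap between the unseen scores and what the model predicts. The article gives neither quantity, so I put no number on it.

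**The case against.** The best case for the protocol has five parts.

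*The dropout video is an addition, not a replacement.* The text introduces it for the drop-out analysis, and the rule to film at T2 has no stated exception. This stands in part. A reader might infer that the protocol cancels week-16 filming for dropouts; it does not say so. What remains is that the one sentence on the primary scale after dropout names only the dropout time, whereas the next sentence, on carers, takes care to keep the schedule.

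*Dropout may mean full withdrawal from assessment.* The term is not defined, and an article may leave that to the full protocol. For patients who refuse all further contact nothing more could be collected. But this is a stated consent and data-collection rule, and as worded it does not ask the patients who only stop sessions for the T2 video.

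*The dropout video is not misused.* A reader might infer that it will stand in for T2, which would amount to carrying the last observation forward. The documents do not support that: it is assigned to the drop-out analysis and that imputation method is rejected.

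*Missing at random may be reasonable.* If dropout follows poor performance that is seen at baseline, t1 or the dropout video, and those scores enter the likelihood, FIML can handle much of it. This stands. It makes the assumption more plausible without supplying an observed T2 value.

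*Feasibility.* A carer completing a form does not show that the patient can be filmed, and patients distressed by failure are the least likely to agree. This also stands: a week-16 request would narrow the gap and would not close it.

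**Conclusion.** The point holds in a limited form. For patients who drop out before week 16, the article provides only a dropout-time assessment on the primary scale while keeping a secondary outcome on schedule. On the natural reading their T2 value is missing and the intention-to-treat comparison leans on missing at random, in a trial whose own ethics section describes performance-related discontinuation that is likelier in TEL.

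A reader might go further and conclude that the trial is underpowered or that the result is biased by a known amount. Neither follows. At the 8.6% loss that the recruitment target covers, power is 0.803; it falls below 80% only at higher losses, which are assumptions here. The direction of bias given above is conditional on the unseen TEL scores being worse than predicted, and its size is unknown. The case for change is that it is cheap and protects the primary outcome.

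**What to change.** In the Statistical analysis section and the matching consent wording:

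1. Ask patients who stop sessions before week 16 to consent to the T2 home video at its planned date, in addition to the dropout-time video.
2. State that all observed T2 values enter the intention-to-treat analysis, whatever number of sessions was received.
3. Keep the dropout-time video for the drop-out analysis, or use it as an auxiliary variable in FIML, and state that it is not a T2 value.
4. Report discontinuations by arm and reason.

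This changes no session schedule and no ground for discontinuation.

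The cost is consent wording and making the filming visit already planned for each patient: about 15 such visits if losses match the margin of 175 over 160, or 35 at an assumed 20% loss (175 × 0.20). Some patients will decline, so dependence on missing at random is reduced and not removed.
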